#### Data collection instruments used

Standardised data collection form for aggregated usage data (completed by project leads); three data collection points within a 3-month period.Questionnaire on individual acceptance and usage for nursing staff, GPs and other healthcare professionals; three data collection points within a 3-month period.FITT-based interview guide used for conducting focus groups; single data collection point.

#### The qualitative data collection comprises

Focus groups with interprofessional teams and semistructured interviews will be conducted to gain deeper insights into experiential contexts, success factors and challenges in the application of telemedical solutions.^30^

### Outcomes

The evaluation aims to achieve a comprehensive understanding of the use, acceptance and effects of teleconsultation in long-term care. Outcome measurement is theory-driven (FITT and UTAUT2) and considers economic, process-related and subjective impact levels.

#### Costs and economic consequences

Both direct and indirect costs will be recorded. In addition, perceived benefits such as time savings or improved coordination will be documented. The presentation follows a CCA.

#### Structures and processes

Structural characteristics of the participating facilities (eg, ownership, staffing ratios, connectivity) will be collected, along with process-related changes in day-to-day care . These include, among others, communication frequency, coordination effort and the temporal sequence of rounds.

#### Usage and feasibility

The practical use of telemedical rounds will be described using aggregated usage data (eg, number and duration of sessions, technical disruptions, documented content). In addition, the perceived fit between technical requirements, task profiles and individual preconditions is analysed, based on the FITT model.

#### User acceptance and perceived benefit

Individual acceptance of teleconsultations will be examined using the UTAUT2 model capturing constructs such as Performance Expectancy, Effort Expectancy, Social Influence and Facilitating Conditions. Furthermore, usage experiences, satisfaction and the subjectively perceived benefit will be considered according to the DeLone & McLean IS Success Model.

### Data analysis

Data analysis follows a mixed-methods approach based on the collected quantitative and qualitative data sources and includes a separate economic assessment in the form of a CCA.

#### Quantitative data analysis

##### Survey data collection

Statistical analysis is performed using R (V.4.4.1), employing the packages gtsummary (V.2.2.0) and stats (V.4.4.1). Quantitative data from standardised questionnaires on individual use and acceptance (nursing staff, physicians), as well as from standardised forms on aggregated usage data, are first analysed descriptively (means, measures of dispersion, frequencies). In addition, regression analyses are used to examine potential associations between individual user characteristics and the core constructs of the UTAUT2 model. The goal is to identify relevant factors influencing the acceptance of telemedical consultations. The questionnaires used (excluding the UTAUT2 instrument) are provided as online supplemental material. The UTAUT2 questionnaire will be made available separately (onlinesupplemental materials 1^4^).

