#### Study objectives

Participatory development of data collection instruments and data flow processes for the evaluation of teleconsultations tailored to the long-term care context.To identify organisational, technical and contextual factors influencing the implementation of teleconsultations in long-term care.Assessment of acceptance and perceived usefulness of teleconsultations among nursing professionals, affiliated physicians and other key interest-holders.Analysis of interprofessional collaboration, with a focus on how teleconsultations shape interprofessional ward round practices.Systematic assessment of direct and indirect costs associated with implementing teleconsultations.Cost–consequence analysis (CCA) of teleconsultations within interprofessional ward rounds in long-term care.

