#### The quantitative data collection will comprise

Structural context data of the participating provider organisations, including the number of sites, staffing ratios, ownership type, geographic location and infrastructural connectivity. These data will serve to contextualise the project sites and to describe the structural framework conditions.Aggregated usage data relating to the number of teleconsultations performed, the type and frequency of technical disruptions, as well as the documented contents and outcomes. In addition, data on costs and implementation efforts will be collected, including time requirements, human-resource requirements, technical support needs and procurement channels. Data collection will be standardised via the project leads to enable a comparative analysis of practical implementation across participating sites.Standardised questionnaires on the subjective experiences and acceptance of the participating interest-holders. Based on the UTAUT2 model, individual assessments, frequency of use and perceived usefulness will be recorded.

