### Qualitative data analysis

The qualitative data from focus groups and semi-structured interviews are analysed using structuring content analysis according to Kuckartz.^33^ Categories are developed deductively based on the FITT perspective (fit between individual, task and technology) and are extended inductively as needed. The aim is to systematically capture subjective experiences, facilitating factors, barriers and contextual influences. The analysis is supported by software (eg, MAXQDA or comparable tools). The interview guide used is available in translated form as online supplemental material 5.

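### The acceptance regressions name only individual user characteristics as predictors, so pooled associations may carry differences between the seven projects

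*Protocol article*

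**What the plan says.** All references are to the protocol article.

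- **The model.** Under Quantitative data analysis, Survey data collection: "regression analyses are used to examine potential associations between individual user characteristics and the core constructs of the UTAUT2 model". The next sentence gives the purpose: "The goal is to identify relevant factors influencing the acceptance of telemedical consultations". No project, technology or setting term is named.
- **The structural data.** Number of sites, staffing ratios, ownership, location and connectivity are collected once, at baseline. Their stated role is: "These data will serve to contextualise the project sites and to describe the structural framework conditions".
- **Other inference.** The Cost–consequence analysis section adds repeated measures ANOVA or a linear mixed model, chosen by time points, scale level and distribution. It names no project, technology or setting factor.
- **Heterogeneity.** Teleconsultations as a potential solution sorts the technical approaches of the seven projects into three types. Study context, complexity and setting says that structural and functional variation may directly affect implementation strategy and engagement. Target groups says that the projects differ markedly in structures, target groups and strategies.

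**The concern.** The goal of the regression covers any factor that influences acceptance, while the named predictors describe only the person. The article itself expects projects to differ in whom they involve and how they work. If, say, one project uses messaging and has younger staff, and messaging is better liked, a pooled regression on age will show an age effect that belongs to the technology.

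The regression is meant to say what drives acceptance, and the Dissemination section promises recommendations to care providers and policymakers. A project or technology difference reported as a user characteristic would point those readers to the wrong lever, for example training for a staff group instead of a different technical solution.

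**Working it through.** The article states no effect size, ICC or respondent number for this analysis, so there is no figure of its own to reproduce. Everything below except the number of projects and α rests on assumptions.

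**Inputs**
- Projects: k = 7 (Study context, complexity and setting).
- α = 0.05, two-sided. The level is stated in the Cost–consequence analysis section; its use for the regressions, and two-sidedness, are assumed.
- Assumed: m = 10 or 20 respondents per project, one response each; project ICC of 0.05, 0.1 or 0.2 for both characteristic and outcome; correlation ρ of 0 or 0.5 between the project effects on the two; no association within project.

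**1. False positives, pooled versus project-adjusted.** Simulation, 3,000 runs per setting. The Monte Carlo standard error near 5% is √(0.05 × 0.95 / 3,000) = 0.4 percentage points.

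| ICC | ρ | Pooled, m = 10 | Pooled, m = 20 | With project, m = 10 / 20 |
|---|---|---|---|---|
| 0.05 | 0 | 4.8% | 5.6% | 4.4% / 5.0% |
| 0.05 | 0.5 | 6.0% | 6.1% | 5.2% / 4.4% |
| 0.1 | 0 | 5.9% | 7.1% | 4.5% / 5.2% |
| 0.1 | 0.5 | 6.8% | 9.7% | 4.3% / 4.8% |
| 0.2 | 0 | 9.1% | 13.3% | 5.3% / 5.2% |
| 0.2 | 0.5 | 14.3% | 22.5% | 5.7% / 4.8% |

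**2. Size of the spurious slope.** With ρ = 0.5 the expected standardised slope is roughly ρ × ICC × (k − 1)/k:
- ICC 0.05: 0.5 × 0.05 × 6/7 = 0.021
- ICC 0.1: 0.5 × 0.1 × 6/7 = 0.043
- ICC 0.2: 0.5 × 0.2 × 6/7 = 0.086

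The simulated means were 0.02, 0.04 and 0.08.

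**3. A concrete example, also assumed.** Three, two and two projects per technology type; acceptance 0, 0.3 and 0.6 SD; mean age 48, 43 and 40; no age effect within type; within-type age SD 10 to 11 years.
- Mean acceptance = (0 × 3 + 0.3 × 2 + 0.6 × 2)/7 = 0.257. Mean age = (48 × 3 + 43 × 2 + 40 × 2)/7 = 44.29.
- Between-type covariance = (0.3 × 43 × 2 + 0.6 × 40 × 2)/7 − 0.257 × 44.29 ≈ −0.85.
- Between-type age variance ≈ 11.6, so total variance is 112 (SD 10) to 133 (SD 11).
- Pooled slope per 10 years = 10 × (−0.85)/112 ≈ −0.076, to 10 × (−0.85)/133 ≈ −0.064 SD, against 0 with technology type in the model.
- With 70 respondents the standard error is about 10/(√70 × 11) = 0.11, so this bias is about 0.6 of a standard error.

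**4. What seven projects can support.**
- With 5 degrees of freedom t = 2.571, so a project-level correlation must reach 2.571/√(5 + 2.571²) = 0.754 for p < 0.05.
- For 80% power it must be about tanh((1.960 + 0.842)/√(7 − 3)) = 0.89.
- If a project-level characteristic is entered in a respondent-level model that ignores clustering, its variance is understated by the design effect 1 + (m − 1) × ICC: 1 + 9 × 0.05 = 1.45 up to 1 + 19 × 0.2 = 4.8.

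**The case against.** **A condensed article may leave covariates to the full plan.** This is fair, and the article does not say that project will be left out. What stands is narrower: the article does state the predictors, a goal wider than those predictors, and a descriptive role for the structural data.

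**The bias is not demonstrated.** Also fair. No section reports how staff mix differs between projects. At an ICC of 0.05 the error rate hardly moves, and the age example is well inside sampling error for 70 respondents. This is a risk of unknown size.

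**Seven projects are too few to model structure.** This stands, and it makes descriptive use of the structural data reasonable. It does not argue against adjusting the individual-level regression for project.

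**Stronger readings that the article does not support**
- A reader might infer that the second objective, "To identify organisational, technical and contextual factors influencing the implementation of teleconsultations in long-term care", gets no quantitative answer. That objective concerns implementation, while the regression concerns acceptance, which is a separate objective. It does not ask for a quantitative answer either. The qualitative strand serves it directly: "The aim is to systematically capture subjective experiences, facilitating factors, barriers and contextual influences". Usage data, including "the type and frequency of technical disruptions", are collected "to enable a comparative analysis of practical implementation across participating sites". UTAUT2 also includes Facilitating Conditions.
- A reader might infer that the qualitative coding frame is deficient because organisation is not one of its starting categories. The frame is extended inductively and has contextual influences among its aims, and the interview guide is in a supplement that is not shown.
- A reader might infer that the survey carries no project identifier. The questionnaires are not shown, so this can only be asked.

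**Conclusion.** The point holds in limited form. The one stated association analysis relates acceptance constructs to individual characteristics alone, while the article describes projects that differ in structure and target group. Read as written, it can attribute a project or technology difference to the person.

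Under the assumed inputs the consequence runs from negligible (5–6% false positives at a project ICC of 0.05) through modest (6–10% at 0.1) to material (9–13% at 0.2 with unrelated project effects, 14–23% with correlation 0.5). Including project brings it to 4–6% throughout. The true ICC, the number of respondents per project and the staff mix are not given, so no single figure can be defended. The change is worth making because it is cheap and project membership should be known. The point does not undermine the study's objectives.

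**What to change.** 1. In Survey data collection, state that the regressions include project as a fixed effect. This is the main adjustment.
2. As a separate, exploratory model, replace project with technology type, and with care setting where a respondent can be classified (the Figure 1 caption shows some projects as mixed). Project effects would absorb any characteristic that is constant within a project, so these terms belong in a model of their own.
3. Tabulate acceptance, usage and disruptions by technology type and by the baseline structural variables. Label these tables, and any project-level association, as descriptive because there are only seven projects.
4. Confirm that each survey response can be linked to its project. The Ethics section mentions participant-managed pseudonymisation codes but does not say whether project is recorded.

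**Cost.** Up to six degrees of freedom. With 70 respondents and one predictor, for example, residual degrees of freedom fall from 68 to 62. Individual-level associations become slightly less precise. No new data are needed if responses already carry a project identifier.

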##### Cost–consequence analysis

As part of the CCA, relevant cost categories will be identified. The quantities of resource consumption will be recorded and corresponding unit costs or prices are assigned.^31 32^ Based on a cost–consequence approach, data on implementation and operational costs, as well as associated consequences, will be collected and recorded in order to enable a transparent comparative assessment. The analysis distinguishes between the following types of costs: direct costs, such as personnel and technology costs; indirect costs, such as training expenses, documentation effort and coordination activities; and intangible costs, such as changes in team climate. In addition, costs will be categorised by phase of occurrence (implementation costs vs operational costs), reflecting when and where the effort arises.

Consequences will include both health-related outcomes (eg, avoided hospital admissions, based on a self-developed questionnaire) and non-health-related outcomes (eg, technology acceptance, based on UTAUT2). In addition, perceived benefits from the perspective of interest-holders will be collected (eg, facilitation of care delivery, time savings, improved interprofessional communication). The aim is to make different cost–consequence relationships visible without monetising the effects. For further statistical analysis, inferential methods will be applied to test significant differences. Significance testing will be conducted at a level of α=0.05. Depending on the time points of measurement, the scale level and the data distribution, either repeated measures analysis of variance or a linear mixed model will be applied.

The CCA will be conducted as part of the formative evaluation. While no control group is included and effects are not monetised, the CCA is designed to provide a structured overview of implementation-related costs and interest-holder-perceived consequences—such as time savings or improved care coordination. This supports a deeper understanding of contextual resource requirements and lays the foundation for future summative and economic evaluations.

### Qualitative data analysis

The qualitative data from focus groups and semi-structured interviews are analysed using structuring content analysis according to Kuckartz.^33^ Categories are developed deductively based on the FITT perspective (fit between individual, task and technology) and are extended inductively as needed. The aim is to systematically capture subjective experiences, facilitating factors, barriers and contextual influences. The analysis is supported by software (eg, MAXQDA or comparable tools). The interview guide used is available in translated form as online supplemental material 5.

### Patient and public involvement

Patients and members of the public were not involved in the design, conduct, or reporting of this study protocol, and no such involvement is planned. The evaluation and data model was developed using a participatory approach with professional interest-holders involved in the project.

## Preliminary results: learnings from the interest-holder analysis

As part of four interest-holder workshops, representatives from all seven projects were continuously involved, including nurse managers, GPs and MFAs (n=average 15–20). The workshops supported a structured discussion of goals, types of data and responsibilities, aligned with the three evaluation dimensions: structure, process and outcome, and at the same time facilitated exchange among project participants. A key result of this participatory phase was the project-specific adaptation of the questionnaire logic, designed to reflect the heterogeneity of the settings (see online supplemental appendix). Furthermore, the collaboration fostered a relationship of mutual trust between the projects and the evaluation team, which is considered beneficial for the subsequent data collection phase.

Due to the heterogeneity of the participating pilot projects, a data model developed jointly and participatively with the project partners is used^34^ (see figure 3). This model enables a tailored assessment of the target groups regarding various cost and consequence categories and incorporates both quantitative and qualitative data. The results of the interest-holder workshops form the basis for the development of a shared data model and for the operationalisation of standardised evaluation parameters. In the second phase, a formative evaluation is conducted, systematically capturing and analysing objective outcome data as well as subjective experiences. The expected results of the study will be presented in a disaggregated format to provide a transparent and differentiated foundation for decision-making in the further development of teleconsultation services in long-term care.

**Figure 3 F3:**
[figure not shown]
Developed data model.

## Discussion

### Potential impact

This development process provided the methodological foundation for a theory-based, context-sensitive and practice-oriented evaluation of highly heterogeneous projects under complex conditions. In line with this focus, the protocol does not aim to evaluate effectiveness. Rather, it details the participatory development of the data model and data collection instruments that will underpin the planned analyses in the next phase of the study. It ensures practical relevance, enhances data quality through shared understanding of the relevance and measurability of key aspects, and embeds the perspectives of the participating projects as a formative element of the study design.

The close involvement of project coordinators and other interest-holders is in line with the MRC framework’s recommendation to evaluate complex interventions through iterative, participatory processes.^21^

In this study, the early and deliberate involvement of interest-holders proved beneficial for the analysis process. At the same time, it also entailed a responsibility to maintain ongoing dialogue with project partners, to incorporate their feedback while maintaining the independence and neutrality of the evaluation. The participatory workshops played a key role in developing a context-sensitive and practice-oriented data model as well as target group-appropriate questionnaires. This co-creative approach not only increased the relevance and acceptance of the instrument but also supported implementation across heterogeneous care settings. A major advantage lies in the improved content validity and closer alignment of data collection with care practice. However, this is balanced by the increased organisational effort and the challenge of integrating diverse perspectives into a coherent evaluation design.^28^

A key insight was that interest-holders in long-term care can act not only as a target group or data source, but also as co-designers of the evaluation. They actively contributed to the structure of the data model (eg, by selecting practice-relevant indicators) and to the wording of the questionnaires (ie, ensuring clarity and feasibility in everyday care settings). This enhanced the transferability between data collection instruments to real-world care environments, but also increased the complexity of the data structure.

In comparison with existing literature on teleconsultations and interest-holder involvement, there is increasing recognition of multiphase, participatory research approaches. For example, Khanassov *et al*,^35^ in their telemedicine study in a primary care setting involving older patients, emphasise the importance of a structured, iterative process across multiple phases in order to address both technical and contextual challenges at an early stage. Similarly, Piau *et al*,^36^ in the DETECT study, a cluster-randomised design in residential care facilities, highlight the relevance of feasibility assessments and context-sensitive implementation strategies, particularly in dealing with neuropsychiatric symptoms among geriatric residents. Both studies underscore the need to conceptualise telemedical interventions not only in technical terms but also from organisational and interdisciplinary perspectives. This is a perspective that our participatory approach consistently embraces and adapts to the specific characteristics of long-term care.

### Ethics

The study was approved by the responsible ethics committee of the Eberhard Karls University of Tübingen (Project number 110/2025). Participation in all data collection activities (interviews, focus groups and online surveys) is voluntary and requires written informed consent. Depending on the mode of data collection, different GDPR-compliant data protection measures (General Data Protection Regulation) are applied, including participant-managed pseudonymisation codes for online surveys. Personal data are processed strictly separately from study data and are not linked to particularly sensitive information. Data processing is carried out exclusively on ISO 27001-certified systems. The online surveys are conducted using the SoSci Survey platform, which meets all required security and data protection standards. This is a non-interventional observational study that does not interfere with existing care or implementation processes. Potential burdens due to time requirements are mitigated through participatory design of the data collection instruments and flat-rate compensation for participants. Additionally, modifications to the data collection instruments resulting from interest-holders’ feedback are implemented and submitted to the ethics committee as an amendment.

